## Abstract

**Background:**

While the emergency department (ED) is often a first point of entry for children and youth with mental health (MH) concerns, there is a limited capacity to respond to MH needs in this setting. Child MH systems are typically fragmented among multiple ministries, organizations, and providers. Communication among these groups is often poor, resulting in gaps, particularly in transitions of care, for this vulnerable population. The evidence-based Emergency Department Mental Health Clinical Pathway (EDMHCP) was created with two main goals: (1) to guide risk assessment and disposition decision-making for children and youth presenting to the ED with MH concerns and (2) to provide a streamlined transition to follow-up services with community MH agencies (CMHAs) and other providers. The purpose of this paper is to describe our study protocol to implement and evaluate the EDMHCP.

**Methods/design:**

This mixed methods health services research project will involve implementation and evaluation of the EDMHCP in four exemplar ED-CMHA dyads. The Theoretical Domains Framework will be used to develop a tailored intervention strategy to implement the EDMHCP. A multiple baseline study design and interrupted time-series analysis will be used to determine if the EDMHCP has improved health care utilization, medical management of the MH problems, and health sector coordination. The primary process outcome will be the proportion of patients with MH-specific recommendations documented in the health record. The primary service outcome will be the proportion of patients receiving the EDMHCP-recommended follow-up at 24-h or at 7 days. Data sources will include qualitative interviews, health record audits, administrative databases, and patient surveys. A concurrent process evaluation will be conducted to assess the degree of variability and fidelity in implementation across the sites.

**Discussion:**

This paper presents a novel model for measuring the effects of the EDMHCP. Our development process will identify how the EDMHCP is best implemented among partner organizations to deliver evidence-based risk management of children and youth presenting with MH concerns. More broadly, it will contribute to the body of evidence supporting clinical pathway implementation within novel partnerships.

**Trial registration:**

ClinicalTrials.gov (NCT02590302)

## Background

Approximately 80 % of children and youth with mental health (MH) problems do not receive any MH services [1–3]. However, this seems to be impacting emergency departments (EDs), which are a commonly used access point for care. Due to the scarcity of child and youth MH services, EDs have increasingly become the place that families present for help. In its baseline scorecard for child and youth MH within Ontario, Canada, the Institute for Clinical Evaluative Sciences (ICES) reported marked annual increases in ED presentations between 2009 and 2012 among youth for anxiety, mood, and substance abuse disorders [4]. At one Canadian ED, visits for MH concerns among children and youth increased, more than 50 % increase from 2010 to 2011 [5], far exceeding the 15 % increase in overall patient visits documented in the hospital administrative database.

Although families attempt to access treatment and services in these settings, EDs are ill equipped to manage these pediatric MH problems. EDs typically lack standardized MH screening tools and pediatric MH expertise. In addition, with the complex and fragmented MH systems across North America [3, 6], many EDs lack defined, reliable, and integrated referral processes to appropriate community resources. Therefore, ED clinicians have difficulty identifying the appropriate MH services to which to refer patients for follow-up care [7].

To address these concerns, a group of Canadian hospital and community-based professionals was commissioned by the Provincial Council on Maternal Child Health in Ontario to create a clinical pathway, known as the Emergency Department Mental Health Clinical Pathway (EDMHCP) for children and youth presenting with MH problems (see Fig. 1). The EDMHCP is designed to (i) improve early identification and intervention for CYMH issues, (ii) provide more timely access to community MH services, and (iii) reduce service gaps for vulnerable children and youth. It defines a standardized approach to risk assessment and disposition decision-making and while improving access to appropriate needs-based MH care [8]. Finally, the EDMHCP aims to provide a seamless transition of care for children/youth and caregivers between the ED, outpatient hospital services and community MH agencies (CMHA), with tailored linkages to community resources through the HEADS-ED screening tool [9] incorporated within the pathway.

**Fig. 1 Fig1:**
[figure not shown]
Emergency Department Mental Health Clinical Pathway algorithm

The overall aim of our project is to implement and evaluate impact of the EDMHCP in specific settings and to evaluate the implementation process. The purpose of this paper is to document the protocol for this 3-year mixed methods health services research project. Research objectives for this study are to:Implement the EDMHCP using a theory-driven, evidence-based approach. The pathway will be implemented in four dyads of organizations, each dyad comprising an ED and an associated CMHA.Evaluate clinical pathway effectiveness through measurement of process and service outcomes. Our hypothesis is that a successfully implemented EDMHCP will lead to improved process and service outcomes.Conduct a process evaluation of the pathway implementation strategy to assess the fidelity of the intervention delivered against the outcomes observed.

## Methods/design

The protocol for this MH project was adapted from a recent ED clinical pathway implementation protocol [10]. Collaborating with site partners, a theory-based and tailored intervention strategy will be developed to implement the EDMHCP within each ED-CMHA dyad. A concurrent process evaluation will be conducted to assess the implementation strategy. For this protocol, we completed the CONSORT 2010 checklist for randomized trials [11].

### Sampling

#### Setting and site selection

To assess EDMHCP feasibility in various settings, implementation will occur in a staggered process in four Ontario exemplar ED-CMHA dyads with different patient populations and workflows that do not currently utilize clinical pathways. Our exemplar ED sites include a pediatric specialized center with an annual patient census of 70,000, a high-volume community urban hospital (annual patient census 75,000), a low-volume rural hospital (annual patient census 25,000), and a high-volume general hospital in a smaller community (annual patient census 60,000).

#### Inclusion/exclusion criteria

To begin, commitment to the implementation intervention by an administrative lead on behalf of each hospital and CMHA will be required. The EDMHCP has specific inclusion/exclusion criteria for patients presenting to the ED, which may be modified at each site based on organizational requirements. Inclusion criteria for patient participants include (1) ages ≥6 and <18 years, (2) ED presentation within a selected 8-month implementation period, (3) MH presenting complaint, and 4) proficiency in English or French. Exclusion criteria include (1) highest priority triage designation (resuscitation), (2) medically unstable patients, (3) intubation/intensive care required, and (4) direct admission to hospital for ongoing medical management and observation. Patients who are stable but require medical management are eligible for the pathway once they are clinically able to participate in a MH assessment in the ED (see Fig. 1).

#### Participants

Participants within each study site include ED staff and physicians, CMHA clinicians, and administrators, as well as patients (and their caregivers) presenting with MH concerns. Site champions will be identified for optimal local implementation.

### Intervention strategy

As illustrated in Fig. 2, our intervention strategy will build on core components with findings from site visits and qualitative interview findings to identify relevant behavior change techniques for our tailored intervention strategy.

**Fig. 2 Fig2:**
[figure not shown]
Intervention strategy

#### Core components

Based on experience in related provincial and regional implementations [12–15], we have provisionally selected core intervention components, as listed in Table 1. Engagement of respected and influential champions at each site is a critical element in promoting and maintaining local interest in the pathway. Additional components include education sessions, website support, posters, and reminders. Currently, an implementation toolkit for the EDMHCP is readily available online (http://www.pcmch.on.ca/health-care-providers/paediatric-care/pcmch-strategies-and-initiatives/ed-clinical-pathways/) [8]. These instructions, measures, and training materials will be tailored for each site and hosted online during the implementation phase on the HEADS-ED website [16]. While the study team will provide guidance and ongoing support, site members will deliver relevant activities to ensure a realistic assessment of requirements for this and future implementations.

**Table 1 Tab1:** Implementation strategy core components

Core component	Description
Local site champion teams	ED physician or staff (nurse educator, ED nurse)
	CMHA clinician or administrator
Hospital and CMHA Commitment	Facilitation through hospital approval processes
	Prioritization within other hospital initiatives
Site visits	Assessment of local ED culture, organization, and feedback on clinical pathway usability (human design factor analysis)
Ongoing site support	Bimonthly teleconferences with site teams
Education	Train-the-trainer workshops
	HEADS-ED training videos
Website support	Resource materials
	Study support
Posters/reminders	Clinical pathway-specific visual tools

#### Theory-based design with knowledge user input

Further aspects of our intervention strategy will be based on the Theoretical Domains Framework (TDF), which consists of a set of conceptual determinants and associated theoretical constructs that are believed to influence behavior and stimulate behavior change [17, 18]. The TDF provides a useful approach to identifying relevant behavioral determinants and designing interventions that will address these [19]. We have successfully conducted TDF-based focus groups with various urban and rural ED teams on implementing the HEADS-ED screening tool [7], an integral component of the EDMHCP. For this study, additional TDF focus groups, with up to 10 participants, will be conducted at each CMHA to elicit perceptions related to adopting the EDMHCP. Further guiding our strategy, we will assess organizational readiness and relevant factors for change through TDF-guided key informant (KI) interviews with one administrator at each site. All interviews will be audiotaped and transcribed for analysis.

#### Site visits

Implementation will begin with site visits to further assess organizational issues within CMHAs and EDs, such as intake and flow of pediatric patients, specific and shared roles of health providers, and pathway fit and acceptability. Infrastructure requirements and implementation readiness will also be assessed. A structured site visit form will be used to take notes and guide visits at each ED or CMHA.

#### Intervention mapping

We will conduct a mapping exercise to link relevant behavioral determinants among health providers identified through the qualitative interviews. We will then tailor our core strategy by applying known taxonomies of behavior change techniques [20, 21] to identify and select appropriate modes of delivery for a multifaceted intervention strategy that would go beyond simply educating for change. For example, methods may include facilitation, nudging, or systems change. Feasibility and practicality will be important considerations to ensure implementation success.

#### Ongoing support and communication

Ongoing support will be provided to expedite pathway implementation and mitigate delays due to other organizational priorities. We will communicate monthly with site champions to support progress during implementation and every 2 months in the post-implementation phase to ensure sustainability. The project coordinator will communicate regularly to ensure target dates are met, using a process log to track reasons for delays that will be explored further in the post-implementation interviews.

### Project phases

The project phases and designated timelines are outlined in Table 2. Once REB approval is secured at each site, the *pre-implementation phase* will proceed with the site readiness visits and qualitative interviews that will determine the final tailored intervention strategies. The *implementation phase* for each dyad begins with a process to secure a written memorandum agreement between the ED and CMHA to ensure clarity of responsibilities and expectations integral to the pathway. Implementation will proceed as per the tailored intervention strategy. Completed pathway implementation requires, at a minimum, the following: EDMHCP site customization and committee approvals, delivery of at least two educational workshops for each organization, and EDMHCP availability in the ED. We have designated an 8-month period for EDMHCP implementation within each dyad. Following initiation within the first dyad, subsequent dyads will begin implementation in a staggered pattern every 3 months to allow for optimal study team support and incorporating learning from experience with previous dyads. In the *post-implementation phase*, qualitative interviews will explore experience with the implementation and site audits will be done to assess implementation status. We have defined the data collection periods as follows: (i) post-implementation, as the consecutive 9-month span that follows implementation completion plus an initial 3-month “settling in” time and (ii) pre-implementation, as a similar 9-month span prior to the intervention.

**Table 2 Tab2:** Description of project phases

Project phase	Duration	Activities
Pre-implementation	6 months	Site recruitment and REB approvals
		Project launch team meeting
		Site readiness visits
		Qualitative interviews and analysis
		Intervention development
		Site champion training
Implementation	17 months (8 months per dyad)	Site customization
		Forms approvals
		Clinical pathway training
		Adoption and feedback
Post-implementation	12 months	Post-implementation site visits
		Qualitative interviews and analysis
Data collection and analysis	4 months	Chart audits
		Chart to administrative database linkage
		Quantitative data analysis
Follow-up	2 months	Project partner meeting: review of findings
		Wrap-up and dissemination

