### Analysis

#### Quantitative analysis

Descriptive statistics (means and standard deviations for continuous variables or medians with interquartile ranges) will summarize EDs, CMHAs, and patient characteristics. Frequencies and proportions for categorical variables will be reported. We will use a multiple baseline study design and conduct interrupted time-series analysis using segmented regression models, adjusting for site, with ARIMA autocorrelation structure [25–27] to evaluate whether the EDMHCP has resulted in improved health care utilization, medical management, and health sector coordination. Two-sided *p* values less than 0.05 will be considered statistically significant. Model estimates will be tabulated, together with 95 % confidence intervals. We will also calculate hospital level summary measures including proportions in the pre- and post-intervention periods at each site and referred to each CMHA. An unweighted mean of the change from pre- to post-intervention will be calculated for each hospital ED. The main effect measure will be calculated as the difference between the mean changes in intervention.

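### No post-implementation data coincide with pre-implementation data in another dyad, so the multiple baseline design as windowed has no concurrent contrast between dyads

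*Protocol article*

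**What the plan says.** The Background objectives fix the number of units: "The pathway will be implemented in four dyads of organizations, each dyad comprising an ED and an associated CMHA".

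Project phases fixes the timing:
- Length of implementation: "We have designated an 8-month period for EDMHCP implementation within each dyad". Table 2 gives the whole phase as "17 months (8 months per dyad".
- Stagger: "subsequent dyads will begin implementation in a staggered pattern every 3 months". The reasons given are study-team support and learning from earlier dyads.
- Post window: "post-implementation, as the consecutive 9-month span that follows implementation completion plus an initial 3-month" settling-in time.
- Pre window: "pre-implementation, as a similar 9-month span prior to the intervention".

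Health record audits confines chart abstraction to alternate weeks within those two windows. Quantitative analysis names the design and model: "We will use a multiple baseline study design and conduct interrupted time-series analysis using segmented regression models", with adjustment for site and an ARIMA error structure. The same paragraph then defines a main effect measure from unweighted pre-to-post changes per hospital. No section describes a control site or an audit of the months between the windows.

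**The concern.** A multiple baseline design improves on a single before-and-after series because some units are still in baseline after others have switched. Those units show what calendar time alone would have done. If no unit is observed in baseline while another is observed after the switch, the staggered starts add no such comparison. The only protection against secular change is then the extrapolated pre-trend.

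At stake is what a positive result would mean. A change common to all sites, such as a province-wide shift in services, documentation practice or coding that falls between the two blocks of data, would move every dyad from its pre level to its post level just as the pathway would.

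**Working it through.** **Inputs** (Background objectives; Project phases): 4 dyads, stagger 3 months, implementation 8 months, settling-in 3 months, both windows 9 months. Month 0 is dyad 1's implementation start. Dyad k starts at S = 3(k − 1), so at months 0, 3, 6 and 9.

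**Reproducing Table 2.** Implementation phase: 3 × 3 + 8 = 17 months, as printed. Post-implementation phase: 3 + 9 = 12 months, as printed. These confirm the implementation and post lengths. They do not confirm where the pre window ends.

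**Windows.** Pre = [S − 9, S]. Post = [S + 8 + 3, S + 20].

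| Dyad | Pre | Post |
|---|---|---|
| 1 | −9 to 0 | 11 to 20 |
| 2 | −6 to 3 | 14 to 23 |
| 3 | −3 to 6 | 17 to 26 |
| 4 | 0 to 9 | 20 to 29 |

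**Overlap.** For post of dyad i and pre of dyad j, overlap = max(0, smaller end − larger start). It is 0 for all 12 ordered pairs. The gap within a dyad is 8 + 3 = 11 months and the total stagger is 3 × 3 = 9 months. Since 9 < 11, no pair can overlap, and months 9 to 11 hold no data from any dyad. With these windows, overlap would need a stagger above 11/3 = 3.67 months.

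**What the segmented model still does.** I used monthly points with equal weight, site intercepts, one common linear trend and a level change.
- The design matrix has rank 6 of 6, so the level change is estimable, and a linear drift of any size biases it by 0.
- Cost in precision: the midpoints of a dyad's windows are 20 months apart (−4.5 and 15.5 for dyad 1). Within a dyad, the sum of squares of time is 2 × 60 + 18 × 10² = 1,920. That of the pre/post indicator is 18 × 0.25 = 4.5, and the cross-product is 18 × 10 × 0.5 = 90. So r² = 90² / (1,920 × 4.5) = 0.9375, and the variance inflation is 1/(1 − 0.9375) = 16. The standard error is 4 times that of a comparison without a trend term.
- A common 10-point step between months 9 and 11 coincides with the pre/post indicator in every observation, so it appears as a 10-point pathway effect. In the same fit, a 10-point step at month 3 gives a bias of about 0, and one at month 15 about 2.8 points.

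**What the main effect measure does.** It has no trend term. With midpoints 20 months apart, a drift of d points per month enters as 20d. For illustration only, d = 0.25 would give 5 points with no pathway effect.

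**The case against.** The strongest reply is that the plan does not rest on a concurrent comparison. It specifies segmented regression, each dyad's own pre-trend serves as its counterfactual, and no passage promises a concurrent control. This largely stands. A reader might infer that every secular change is fully confounded, or that the study is simply an uncontrolled before-after comparison. For the planned regression that is too strong, since linear change is removed and a step well away from the gap is only partly absorbed. A reader might also infer that the effect cannot be estimated. That is true only if calendar-month effects are added to dyad effects (rank 39 of 40 columns), and the protocol names no such model.

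It is tempting to cite the rising ED presentations in the Background as evidence of bias. Those are visit counts, whereas both primary outcomes are proportions, and a steady annual rise is the kind of trend the regression handles.

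The timing also depends on a reading. The end date of the pre window is not fixed. If settling-in lay inside the 9 months, dyads 1 and 4 would overlap by 1 month, but Table 2's 12 months speak against that. If the pre window ran up to the end of implementation there would be real overlap, but the text does not say so. Actual completion dates may also differ from 8 months. With starts as planned, dyad 1 would have to complete before month 6 (6 + 3 = 9) to overlap with dyad 4's baseline.

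Finally, one might suppose that auditing every month repairs the design. With the preparation months modelled as their own phase, direct post-versus-baseline overlap remains 0 months.

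**Conclusion.** The point holds in a limited form. On the natural reading, with each pre window ending at the start of implementation and dyads keeping to schedule, post/pre overlap between dyads is 0 months. The multiple baseline label in the Abstract and in Quantitative analysis therefore describes a contrast that the data will not contain.

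The segmented regression remains usable against linear change. It extrapolates across 11 months without data, with a variance inflation of about 16 (equal monthly weights, common linear trend, independent errors). A common step between months 9 and 11 is fully aliased with the pathway under any model fitted to these windows, and other non-linear change is removed only in part.

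The weakest element is the main effect measure. I read it as the average unweighted pre-to-post change, because the text names no second group to subtract. On that reading it has neither a trend adjustment nor a concurrent comparator.

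The documents do not show that secular change of this kind will occur. They show only that the design could not detect it.

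**What to change.** **Main change.**
1. Make the trend-adjusted segmented-regression estimate the main effect measure, and keep the unweighted pre-to-post change as a descriptive summary.
2. Describe the design as a staggered interrupted time series without concurrent control.
3. State that step or other non-linear secular change between the windows cannot be separated from the pathway.
4. State the end date of the pre window.

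This costs wording and a less precise headline estimate. It needs no further data.

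**Alternative, if the multiple baseline claim is to be kept.** Define the interruption as the recorded date on which the pathway becomes available in the ED, and run the retrospective chart audit up to that date. If that is month 8 of each dyad's implementation, pre data end at months 8, 11, 14 and 17. Overlap with post data is then 14 − 11 = 3 months (dyad 1 post, dyad 3 pre), 17 − 11 = 6 (dyads 1 and 4) and 17 − 14 = 3 (dyads 2 and 4), which is 12 dyad-pair months in all. Earlier or later availability changes these figures.

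The downside is that late pre months include training and customization, so some contamination is likely. A sensitivity analysis should check this. Moving the 9-month window adds no months of audit, whereas lengthening it adds up to 8 months per dyad. Table 4 also lists telephone follow-up as a source for the primary service outcome, and that part cannot be recovered by a retrospective audit. The trial was in its pre-implementation phase when the article was written, so either change could be made without altering the rollout.
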